# Clinical efficacy of mandibular complete dentures with a resilient liner: study protocol for a multicenter randomized controlled trial

**DOI:** 10.1186/s13063-022-06657-3

**Published:** 2022-09-02

**Keywords:** Randomized controlled trial, Complete denture, Edentulism, Resilient liner, Reline, Patients’ general satisfaction, Masticatory performance, Oral health-related quality of life

## Abstract

**Background:**

During restoration of poorly fitting complete dentures (CDs) in edentulous patients, liners are used to reconstruct the concave surfaces of CDs with a new base material. These relining materials are classified into resilient liners (RLs) and non-resilient liners (NRLs), but the clinical effects of these liners and their selection criteria remain unclear. The purpose of this study is to evaluate the clinical efficacy of relining mandibular CDs using RL and NRL and to conduct a follow-up study.

**Methods:**

The study is currently being conducted at eight centers, and a parallel-group randomized controlled trial (RCT) is underway. One hundred thirty-two edentulous patients with poorly fitting mandibular CDs will be assigned to two groups based on whether they will receive RL or NRL. Participants will have an RL or NRL applied for relining their CDs using an indirect method of dynamic impressions. Data will be recorded at 1 week and 3, 6, and 12 months after denture delivery. The primary outcome will be assessment of the patients’ general satisfaction by using a 100-mm visual analog scale (VAS). Secondary outcomes will be measured as patient-reported outcomes, including food intake status and oral hygiene-related quality of life. Masticatory performance and the number of sore spots on the oral mucosa will also be recorded. Comparisons between the two groups and within-subject comparisons of pre- and post-intervention measurements will be conducted.

**Discussion:**

For dentists and prosthetic researchers in Japan, this RCT will provide information on the clinical efficacy of RL materials in comparison to RNL in CD wearers. The new evidence regarding the use of RL materials in an aging population will also be useful to dentists in other countries in their routine clinical practice.

**Trial registration:**

This clinical trial has been registered at the University Hospital Medical Information Network (UMIN) Center (UMIN000041950).

## Background

The aging of the global population, especially in developed countries, has led to an increase in the number of edentulous patients [1, 2]. In dental treatment, complete dentures (CDs) are generally the first choice to restore routine masticatory function in edentulous patients. However, due to the significant alveolar bone resorption and mucosal thinning caused by a range of oral diseases in the elderly, in clinical practice, mandibular CDs cannot be used satisfactorily in many cases owing to movement and pain. Recently, implant-supported overdentures have been considered as one of the options for maintaining and stabilizing dentures [3, 4], but due to systemic diseases, inability to visit the hospital, and cost issues, most patients often choose to repair their existing CDs [5]. The reline method is generally used for repairing a non-retentive CD. According to the Glossary of Prosthodontic Terms-9 [6], relining is defined as a procedure of resurfacing the concave surface of a CD with a new base material to precisely fit the denture base. Relining materials are classified into resilient liners (RLs) and non-resilient liners (NRLs) according to their chemical structure.

Randomized clinical trials (RCTs) have been conducted to investigate the clinical effects of newly fabricated CDs with RL materials in edentulous patients. These trials reported that the cushioning effect reduced pain and pressure ulcers during occlusion, improved patient satisfaction and masticatory performance, and reduced the number of denture adjustments [7–13]. However, no studies have investigated the superiority of CDs with RL materials over conventional CDs with NRL materials in cases of poorly fitting CDs. Therefore, we plan to conduct an RCT including the following centers throughout Japan: Tokyo Medical and Dental University, Nihon University School of Dentistry at Matsudo, Tsurumi University, Kanagawa Dental University, Aichi Gakuin University, Tokushima University, Nagasaki University, and Kagoshima University. This eight-center RCT has external validity and has been named the “mandibular CDs with resilient liner trial II” (MCORT II). The purpose of MCORT II is to evaluate patients’ general satisfaction with the relining of mandibular CDs using an RL material versus the relining of mandibular CDs using an NRL material, and to conduct a follow-up study.

## Methods/design

### Trial design

This trial is being organized by the Japanese Society for Denture Care. The trial has been developed by KK, the sponsor of the study, and conducted at eight centers (university hospitals). The trial is designed as a multicenter randomized parallel trial comparing patient satisfaction with mandibular CDs using RLs and that with mandibular CDs using NRLs, with a superiority test as the framework of this trial. Several coordinators are in close contact with the investigators at each university. Each university has an investigator and a dentist as the operator. The coordinator randomly assigns and manages the schedules of participants and investigators. The investigator obtains documented informed consent from the potential participant. They are then trained to evaluate the results of the clinical trial before measuring the data. The dentists who provided the denture treatment are not allowed to be investigators for this trial. This trial has been registered with the University Hospital Medical Information Network (UMIN) Center (UMIN000041950) on 10 October 2020.

### Organization

The coordinating center (TCC), data monitoring committee (DMC), and the steering committee (TSC) have been established for this clinical trial.

TCC consists of the chief coordinator (NH) and the coordinators (SK, YS), who are in constant contact with each other. The role of the center is to allocate patients and study design, to oversee the collection, management, analysis, and interpretation of data, and to submit the results to the steering committee.

The DMC consists of dentists who are not involved directly in this clinical trial as well as experts other than dentists. The role of the DMC is to conduct an audit of progress (report submission) to the coordinating center every 2 months and report the results to the steering committee.

TSC consists of the coordinator, the investigators and dentists from each university, and members of the DMC. The role of this committee is to audit the progress of the trial, report adverse events, deliberate and decide on important changes to the study protocol including study discontinuation, and have final authority over the trial. TSC is scheduled to meet four times a year. In addition, the contents of TSC meetings are always reported to the sponsor, and the sponsor is obligated to report annually to the funder (the Japan Society for the Promotion of Science) on progress and results to date.

### Participants

The trial will be performed at the dental hospitals of eight universities in Japan. The recruitment and treatment protocols of the present trial have been approved by the ethical review committee of the following universities: Tokyo Medical and Dental University (Register No. D2020-058), Nihon University School of Dentistry at Matsudo (Register No. EC2-042), Tsurumi University (Register No. 1840), Kanagawa Dental University (Register No. 733), Aichi Gakuin University (Register No. 612), Tokushima University (Register No. 3855), Nagasaki University (Register No. 21041910), and Kagoshima University (Register No. 200313).

The inclusion criteria are as follows: (1) edentulous patients who wanted to have their mandibular CDs repaired and (2) patients who provided written informed consent for this study. The exclusion criteria are as follows: (1) patients with physical or mental problems, (2) patients who cannot hear or read Japanese, (3) patients with dietary restrictions, and (4) patients with oral dyskinesia.

### Sample size calculation

The general satisfaction of patients will be measured as the 100-mm visual analog scale (VAS) score after 3 months of relining. The use of an RL material will be judged to be clinically effective when the VAS score of patients having CDs with RL is 15 mm higher than that of patients having CDs with NRL. Thus, the difference between the means of the two groups is set to 15 mm. The sample size is calculated using *α* = 0.05 and *β* = 0.8, based on the standard deviation of the overall satisfaction obtained in a previous study (CDs with RL: 26.3, CDs with NRL: 31.4) [7]. However, assuming that 10% of the participants would drop out, the target number of participants has been set at 132.

**Fig. 1 Fig1:**
[figure not shown]
Flow diagram showing the protocol of interventions

### Intervention

The intervention for this trial will be the application of an RL material (Reline 2 Extra Soft; GC, Tokyo, Japan) or an NRL material (Rebase III [Normal]; Tokuyama Dental, Tokyo, Japan) to the mandibular CD. This trial uses an indirect lining method with the application of dynamic impression. Tissue conditioner (Tissue Conditioner II Soft; Shofu, Kyoto, Japan; Tissue Conditioner; GC, Tokyo, Japan) will be used for recording the dynamic impression. All prosthetic procedures will be performed by a prosthodontist with at least 5 years of experience. In principle, the indirect method should be performed by a dental technician. The technique used is as follows:A dynamic impression is made using a tissue conditioner on the CD to be indirectly relined. The dynamic impression should be recorded when the patient does not complain of pain during mastication. Considering the surface properties of the tissue conditioner, an interval of approximately one week between uses is appropriate.A super-hard plaster (New Fuji Rock; GC, Tokyo, Japan) is poured on the dynamic impression surface to make a plaster model, which is flasked for denture processing.The flask is opened, the tissue conditioner is peeled off from the mucosal surface of the model, and the mucosal surface of the denture base is trimmed to create space for the reline layer. The thickness of the reline layer is approximately 2 mm.After applying the adhesive material according to the manufacturer's instructions, the CD is lined with the relining material (RL or NRL), cured, morphed, and polished. The relined CD is then delivered to the patient. Post-denture delivery follow-up appointments will be scheduled, and any necessary adjustments will be carried out.

### Outcomes

The basic patient information recorded will include age, sex, years of denture use, and number of dentures fabricated. In addition, treatment difficulty index measurements [14, 15] and evaluation of used dentures [16] will be performed. Since patient satisfaction with CDs is a clinically important factor for evaluating the therapeutic effect of CDs with RL, the primary endpoint will be patients’ overall satisfaction with the CDs, which will be determined using a 100-mm VAS [17]. Patient satisfaction will be assessed comprehensively using a questionnaire containing eight assessment items: general satisfaction, ease of speaking, ease of cleaning, retention, stability, comfort, and esthetics. Participants will be asked to rate their satisfaction with each item in the questionnaire by using a 100-mm VAS to evaluate their current CDs. Data will be recorded as continuous variables at 1-mm intervals by using calipers from the left end. Overall patient satisfaction will be measured four times: at baseline, 7 days, 3 months, 6 months, and 1 year.

In addition, to comprehensively understand the clinical effect of CDs with RL material, the Oral Health Impact Profile for edentulous subjects (OHIP-EDENT) [18], masticatory ability [19, 20], food intake [21, 22], and the location and number of mucosal pressure ulcers will be examined as secondary outcomes. Photographs of mucosal pressure ulcers will be shared among investigators to adequately calibrate assessments of the mucosal surface (Fig. 2).

**Fig. 2 Fig2:**
[figure not shown]
Photographs of pressure ulcers caused by representative dentures used for investigator calibration

### Trial schedule

The trial schedule is outlined in Table 1.

**Table 1 Tab1:**
[figure not shown]
Schedule of subjects and investigators

#### Initial visit (baseline)

After receiving informed consent from the patient, the investigator requests a group allocation to the coordinating center. Once the patient has been assigned to a group, a dentist is selected to be in charge. At that time, basic patient information is collected and patient satisfaction and OHIP-EDENT are assessed.

The dentist-in-charge adjusts the jaw-type complete denture in use, if necessary, and schedules the next appointment.

#### Second visit

The investigator evaluates the patient's masticatory performance and food intake. The dentist performs a dynamic impression with tissue conditioner to initiate the intervention.

#### Third visit

The dentist-in-charge places the denture in use once the pain is gone.

#### Fourth visit

The dentist-in-charge places the mandibular CD with a resilient liner in the mouth.

#### A week after the denture is placed

The investigators measures the location and number of mucosal pressure ulcers, patient satisfaction, OHIP-EDENT, and chewing ability.

#### After 3, 6, and 12 months of wearing

The investigators evaluates patient satisfaction, chewing ability, OHIP-EDENT, and food intake.

### Response to adverse events

The investigator, him or herself a dentist, will carefully monitor the occurrence of adverse events. If an adverse event occurs, appropriate measures will be taken and, in principle, the patients will be observed until the event disappears. The type of adverse event, date of occurrence (or date of hospital visit when discovered), details of treatment (continuation, discontinuation, etc.), course of the adverse event, and details of any causal relationship with the resilient liner will be promptly reported to the steering committee. Observations will continue up to 1 year after the application of the resilient liner and will continue throughout the study period.

In this study, there is no anticipated harm and compensation for trial participation.

### Discontinuation of the trial

If any of the following discontinuation criteria are met during the study period, that individual patient will be discontinued promptly at the discretion of the principal/participating investigator: (1) when the subject withdraws consent, (2) when the subject moves to a new hospital due to relocation or stops coming to the hospital for other reasons, (3) when a subject develops symptoms that make it undesirable to start the study, (4) if it is discovered after the start of the study that the subject does not meet the selection criteria or violates the exclusion criteria, and (5) when it is determined that continuation of the study is not desirable for the patient for any other reason.

When the decision is made to terminate the study, the coordinators first report the decision to the steering committee, and if a change in protocol is involved, a breach report is also submitted. The steering committee then notifies the sponsor and the coordinators of each university.

### Data handling

The study coordinators and dentists at each university will identify the patients using registration numbers and initials during the duration of data preparation and handling. They will also take into consideration the protection of patient confidentiality. All of the personnel involved in this study will not be permitted to divulge, without justifiable cause, any confidential information about the individuals involved in the study.

The collected data from each university will be gathered and stored at the coordinating center (Kanagawa Dental University). The chief coordinator will review the collected data, after which the coordinator will perform an interim analysis and then a final analysis. Based on the results of the interim analysis and the status of data accumulation, the coordinating center will decide on the formal termination of the trial.

All materials used in the study will be stored for 3 years after the completion or discontinuation of the study. In principle, access to the final clinical trial data is limited to the coordinator, but any data required to support the protocol can be supplied on request. This trial does not involve collecting biological specimens for storage.

### Statistical analysis

All the analyses will be performed in accordance with the intention-to-treat principle, and various strategies to account for any post-randomization missing data will be contemplated. The statistical analyses will be performed as follows:Normality will be confirmed by the Kolmogorov–Smirnov test, and either parametric or nonparametric tests will be performed.Between-group comparisons will be made using Student’s *t*-test or Mann–Whitney *U* test, depending on the distribution of the outcome.Within-group comparisons will be performed using the paired t-test or Wilcoxon's signed-rank test, depending on the distribution of the outcome.Chi-square test will be used to test proportions.The significance level will be set at 5% on both sides, and p-values will be adjusted by Bonferroni’s correction to account for multiplicity when more than three groups are compared.

Subgroup analyses will also be performed among the different subpopulations defined by each of the multiple baseline characteristics of the participants in order to study whether the effects of the intervention vary across patient characteristics.

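### The primary 3-month VAS comparison uses one value per patient and no fixed missing-data method, although baseline and 7-day VAS are collected and 10% dropout is planned for

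*Protocol article*

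**What the plan says.** - **Analysis (Statistical analysis section).** All analyses are to follow intention-to-treat. On missing data the same sentence adds only that "various strategies to account for any post-randomization missing data will be contemplated". Between-group comparisons use Student's t-test or the Mann–Whitney test, depending on distribution. No imputation, model or sensitivity analysis is named.
- **Endpoint and time point.** The Outcomes section makes overall satisfaction on a 100-mm VAS the primary endpoint. The Sample size calculation section places it 3 months after relining.
- **Data collected (Outcomes).** "Overall patient satisfaction will be measured four times: at baseline, 7 days, 3 months, 6 months, and 1 year". The sentence counts four occasions and lists five. Either way, a baseline and a 7-day score precede the 3-month score.
- **Expected loss (Sample size calculation).** "assuming that 10% of the participants would drop out, the target number of participants has been set at 132". No time point, arm or reason is attached to the 10%.
- **Routes off study (Discontinuation of the trial).** These include "when the subject moves to a new hospital due to relocation or stops coming to the hospital for other reasons". The article does not say how the 3-month score is handled for such patients.

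**The concern.** A two-sample t-test or Mann–Whitney test needs one number per patient. A patient who attends at baseline and 7 days but has no 3-month score adds nothing to it unless a value is supplied, and the article gives no rule for supplying one. The intention-to-treat promise is therefore not secured for the analysis that matters most.

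The missing patients may not be typical. The trial is open-label, the outcome is self-reported, and a patient unhappy with a reline may be the one who stops attending. If that happens more in one arm, a comparison of those who remain is biased. The 7-day score is the collected measurement most likely to show who was heading that way, and the named tests leave it unused.

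**Working it through.** **1. Reproduce the plan's sample size.** Inputs from the article: "The sample size is calculated using *α* = 0.05 and *β* = 0.8" (0.8 is read as power, the only reading that returns the stated total); "The significance level will be set at 5% on both sides"; "the difference between the means of the two groups is set to 15 mm"; SDs "CDs with RL: 26.3, CDs with NRL: 31.4".

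n per arm = (1.960 + 0.842)² × (26.3² + 31.4²) / 15² = 7.85 × 1677.65 / 225 = 58.5, so 59 per arm and 118 in total.

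118 / 0.9 = 131.1, so 132, as stated. The sizing counts 132 − 118 = 14 patients as giving no primary value.

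Power (normal approximation) is 80.3% with 59 per arm and 84.5% with all 66. The planned loss is paid for in power, so the remaining question is bias.

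**2. Bias if only patients with a 3-month score are compared.** The documents do not give the next inputs, so they are assumptions. Scores are normal with the plan's SDs. Patients leave after the 7-day visit. The correlation ρ between 7-day and 3-month VAS is 0.4, 0.6 or 0.8.

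The lowest 30% of a normal distribution averages 0.3477 / 0.30 = 1.159 SD below the mean. If leavers come at random from the lowest 30% of 7-day scores, their 3-month mean lies 1.159 × ρ × SD below the arm mean. If a fraction p leaves, the mean of those remaining rises by p/(1 − p) times that amount.

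*Similar loss, 10% of each arm, all low scorers.* The arms' shifts nearly cancel:

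bias = 0.10/0.90 × 1.159 × ρ × (31.4 − 26.3) = 0.66ρ, which is 0.3, 0.4 and 0.5 mm.

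*Uneven loss, 15% of the NRL arm from its low scorers and 5% of the RL arm at random (10% overall).*

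NRL shift = 0.15/0.85 × 1.159 × ρ × 31.4 = 6.42ρ

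| ρ | Bias against RL | Complete-case estimate, truth 15 mm |
|---|---|---|
| 0.4 | 2.6 mm | 12.4 mm |
| 0.6 | 3.9 mm | 11.1 mm |
| 0.8 | 5.1 mm | 9.9 mm |

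*Mirror image, 15% low scorers lost from RL and 5% at random from NRL.* The shift is 0.15/0.85 × 1.159 × ρ × 26.3 = 5.38ρ, or 2.2 to 4.3 mm, now in favour of RL.

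*A cruder check without ρ.* With 15% lost in one arm and 5% in the other, and leavers 10 to 30 mm below completers in both, the all-randomised and completer differences differ by (0.15 − 0.05) × 10 to 30 = 1 to 3 mm.

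**3. What the earlier scores recover.** Simulation of the uneven-loss case used 66 per arm, ρ = 0.6, baseline correlation 0.3 with each later score, a 7-day effect 70% of the 3-month effect, and 4,000 trials:

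| Method | Mean estimate (truth 15 mm) |
|---|---|
| Complete case | 11.0 mm |
| Last value carried forward | 16.8 mm |
| Regression on baseline and 7-day VAS, all randomised | 14.9 mm |

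The regression is the equivalent of a likelihood model for this dropout pattern. Its standard error is about 5.2 mm, against 5.3 mm for complete case. Complete-case power falls from 80% to about 56%. The simulated 11.0 mm agrees with the 11.1 mm from the formula.

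**The case against.** The strongest reply is that this is a condensed article. A full protocol exists, an analysis plan may, and the choice of missing-data method usually sits there. That stands for the bare absence of a policy. It does not cover the test the article does fix, which sets aside scores that the trial collects.

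A reader might infer more, and the documents do not support it:

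- *That the tests can only drop patients.* Either test can be run on imputed data, and the missing-data clause foresees strategies of some kind.
- *That the result will not be intention-to-treat.* No complete-case analysis is prescribed. The promise is unsecured, not broken.
- *That the method will be chosen after the data are seen.* The article gives no timing. Simulated type I error of roughly 7% to 8% from taking the best of three strategies assumes deliberate selection of the smallest p-value, which nothing in the text plans.
- *That the sample size is wrong.* It reproduces exactly, and inflating for dropout does not commit the analysis to complete cases.

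It is also fair to say that the uneven-loss pattern is severe and assumed, that its bias runs against RL and so is conservative for a superiority claim, and that loss by 3 months may be below 10% in a 12-month study. These points limit the size of the concern. The conservatism does not hold in general, because the mirror pattern favours RL. The precision gain from the model is small, so the case for it rests on bias.

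**Conclusion.** The concern holds in a limited form. The article pairs a firm intention-to-treat promise with single-value tests and an open-ended missing-data clause, in a trial sized for about 14 missing primary values (if the 10% applies by 3 months).

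The possible harm is bias, not lost planned power. It is under 1 mm if low scorers leave equally from both arms. It is about 3 to 5 mm of the 15 mm target, against RL, if they leave mainly from NRL, and of similar order in RL's favour if they leave mainly from RL. These sizes rest on assumed correlations of 0.4 to 0.8 and assumed dropout patterns; the documents supply neither. The model's advantage holds when missingness depends on the observed earlier scores. The point should be acted on, but it does not undermine the design.

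**What to change.** In the Statistical analysis section, replace the missing-data clause and the primary use of the simple tests with the following:

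- **Primary analysis.** A likelihood-based repeated-measures model of satisfaction VAS in all randomised patients, using every scheduled visit, with arm, visit and arm-by-visit terms. Baseline VAS is adjusted for or constrained equal between arms. The RL–NRL contrast at 3 months is the primary result. The constrained form also keeps patients who have only a baseline score.
- **Secondary.** The t-test or Mann–Whitney test on observed 3-month scores, as now planned.
- **Sensitivity.** One pre-named analysis that lowers the missing 3-month values by stepwise amounts, separately by arm, and reports where the conclusion changes.
- **Timing.** Fix all of this before the interim analysis mentioned under Data handling.

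The cost is revised wording and a little more analysis work, with no new visits, data or patients. The model assumes that missingness is explained by observed scores, and the sensitivity analysis examines that assumption. One check is needed first. The initial-visit section appears to place the baseline VAS after allocation, so using it this way presumes that patients score it before learning their arm.
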